# Effect of an mHealth self‐help intervention on readmission after adult cardiac surgery: Protocol for a pilot randomized controlled trial

**DOI:** 10.1111/jan.15104

**Published:** 2021-11-28

**Keywords:** cardiac surgery, mHealth, patient participation, randomized controlled trial, readmission, representation

## Abstract

**Aim:**

To describe a protocol for the pilot phase of a trial designed to test the effect of an mHealth intervention on representation and readmission after adult cardiac surgery.

**Design:**

A multisite, parallel group, pilot randomized controlled trial (ethics approval: HREC2020.331‐RMH69278).

**Methods:**

Adult patients scheduled to undergo elective cardiac surgery (coronary artery bypass grafting, valve surgery, or a combination of bypass grafting and valve surgery or aortic surgery) will be recruited from three metropolitan tertiary teaching hospitals. Patients allocated to the control group with receive usual care that is comprised of in‐patient discharge education and local paper‐based written discharge materials. Patients in the intervention group will be provided access to tailored ‘GoShare’ mHealth bundles preoperatively, in a week of hospital discharge and 30 days after surgery. The mHealth bundles are comprised of patient narrative videos, animations and links to reputable resources. Bundles can be accessed via a smartphone, tablet or computer. Bundles are evidence‐based and designed to improve patient self‐efficacy and self‐management behaviours, and to empower people to have a more active role in their healthcare. Computer‐generated permuted block randomization with an allocation ratio of 1:1 will be generated for each site. At the time of consent, and 30, 60 and 90 days after surgery quality of life and level of patient activation will be measured. In addition, rates of representation and readmission to hospital will be tracked and verified via data linkage 1 year after the date of surgery.

**Discussion:**

Interventions using mHealth technologies have proven effectiveness for a range of cardiovascular conditions with limited testing in cardiac surgical populations.

**Impact:**

This study provides an opportunity to improve patient outcome and experience for adults undergoing cardiac surgery by empowering patients as end‐users with strategies for self‐help.

**Trial registration:**

Australian New Zealand Clinical Trials Registry (ANZCTR): ACTRN12621000082808.

## INTRODUCTION

1

Readmission is multifaceted, but patient driven, potentially avoidable and costly. When readmission rates have been investigated there are consistent features evident in the literature. Literature is generally focused on the efficacy of readmission rates as a quality of care metric (Kansagara et al., 2011), usually in a variety of settings and medical patient populations (Hansen et al., 2011; Leppin et al., 2014). Models have been devised to predict which patients might be readmitted, why patients might require readmission, and if at risk of readmission, which pre‐discharge, post‐discharge or in‐patient interventions might reduce the risk. In the cardiac surgery domain, interest in readmission risk prediction coincided with interest in readmission as a quality‐of‐care metric and there is a plethora of literature from the United States examining readmission risk. In the Australian and European context there is minimal research focused on reasons for or risk of readmission for cardiac surgical candidates.

The utility of social, environmental and system factors that influence patients’ ability to enact self‐care behaviours or access supports to avoid readmission is also under‐investigated. Similarly, the impact of health literacy, patient participation and shared decision‐making on rates of readmission is not well understood. Models are constructed using retrospective administrative data, real‐time administrative data or less frequently prospective primary data collection. In data from the US there is some consistency in factors that increase readmission risk across cardiac settings and samples, but a key feature of models to date is their poor predictive ability. Models predict mortality with reasonable specificity and sensitivity, not readmission. Very few studies assess the influence of variables that are indicative of overall health and function. Frailty, social determinants of health and informal caregiver support are rarely evaluated (Kansagara et al., 2011). In addition, process factors such as the timeliness of post‐discharge follow up, primary‐care coordination and quality of inpatient care are not featured (Gallagher et al., 2020). It is postulated that patient activation, or patients’ capacity to access and enact post‐discharge care crucial for optimal recovery, may influence rates of representation and readmission.

### Background

1.1

When strategies to reduce readmission rates are explored, interventions are generally in the form of a ‘care bundle’ or explicit actions implemented at a particular time point. Pre‐discharge interventions commonly include patient education, medication reconciliation and scheduling of follow‐up prior to discharge. Post‐discharge interventions include follow‐up phone calls, patient‐activated hotlines, ambulatory care services and home visits (Hansen et al., 2011). There is also a range of bridging interventions designed to impact on transition from in‐patient to primary care. These studies enable us to consider optimal strategies at specific trajectory time points, but systematic review has revealed poor study description, methodological flaws and the use of ‘care bundles’ make it difficult to determine the efficacy of any single intervention on readmission rate reduction (Hansen et al., 2011). Leppin et al. (2014) published a systematic review of interventions for the prevention of readmission that scrutinized features of interventions to determine effect on treatment burden and patients’ capacity to enact burdensome self‐care. These authors concluded that all interventions work to some degree but interventions that support patient capacity for self‐care in the transition from hospital to home are the most effective.

In the cardiac surgery domain, modelling studies have focused on factors that increase risk of readmission and reasons for readmission in American patients with varying levels of readmission risk. Most studies have focused on patients undergoing coronary artery bypass grafts (CABGS). Readmission rates vary widely from 39% in a large multicentre study of patients having surgery in the late 1980s (Steuer et al., 2002) to 6.3% in a low‐risk single centre private sector cohort (Sun et al., 2008). In this relatively homogenous cohort common factors increasing readmission risk are increasing age, female gender, African American race, multiple comorbid conditions and postoperative complications (Hannan et al., 2011; Jarvinen et al., 2003; Vaccarino et al., 2003). Specific studies have also linked additional patient factors including obesity (Rockx et al., 2004), preoperative inflammatory markers (Brown et al., 2013) and diabetes (Stewart et al., 2000) to readmission risk. Few studies have investigated process factors such as ‘off pump’ surgery (Karolak et al., 2007) and ‘fast track’ early discharge (Gooi et al., 2007).

Early discharge has been linked to increased readmission rates into post‐acute care settings and subsequent increased length of stay (LOS) in those settings (Bohmer et al., 2002; Cowper et al., 2007). Acute care facilitates avoid penalty by discharging patients early and admitting them to transitional or sub‐acute care facilities (Lazar et al., 2001). Postoperative LOS is an independent predictor of readmission irrespective of postoperative complications and when LOS in the intensive care unit (ICU) is increased, readmission rates have been reported to be as high as 62% (Lagercrantz et al., 2010). Readmission rates do not differ in studies comparing centres with and without specialist cardiac services (Novick et al., 2007). Very few studies have explored social determinants of health but there has been interest in exploring the effect of mental health on outcome after cardiac surgery, including rates of readmission. Levels of stress, anxiety and depression (Oxlad et al., 2006; Tully et al., 2008) are reliable predictors of poor outcome and increased rates of readmission but are rarely included in models of prediction.

The most common reasons for readmission vary and include arrhythmias 2.4% (Efthymiou & O'Regan, 2011) to 23.1% (Sun et al., 2008), pneumonia or respiratory complications 0.5% (Efthymiou & O'Regan, 2011) to 18%, infection 1.3% (Efthymiou & O'Regan, 2011) to 20% (Cowper et al., 2007) and congestive heart failure 14% (Cowper et al., 2007). Additional reasons reported include constipation, hypotension (Efthymiou & O'Regan, 2011), chest discomfort (Fox et al., 2013), angina and pericardial effusion or tamponade (Sun et al., 2008). In the Australian context Murphy et al. (2008) found living alone was the only independent predictor of readmission in a single centre study of 181 patients of whom 14.4% were readmitted. Another single centre Australian study (Slamowicz et al., 2008) found substantial variability in readmission according to time, where readmission rates were 7% at 7 days, 15.2% at 30 days and 32.3% at 6 months post discharge. In more recent research Fox et al. (2013) found overall readmission was 26.9% when readmission (15%, 95% CI 10.5–13.7) and re‐presentation (11.9%, 95% CI 13.5–16.5) were differentiated. When cohorts include other common types of cardiac surgery, readmission rates rise further. In a multicentre prospective Canadian study of 5158 patients over 10 years, 30‐day readmission rates were 14.9%, 18.3% and 25% for isolated CABGS, isolated valve and combined CABGS and valve surgery, respectively (Iribarne et al., 2014).

Fewer interventions for readmission reduction in cardiac surgery cohorts have been investigated in contrast to those for general medical or surgical patients. An integrative review of preoperative education as a means of reducing readmission found educational materials, methods of needs assessment and specific teaching methods were under‐investigated (Veronovici et al., 2014). Randomized controlled trials of models of care that incorporate a specialist nurse or nurse practitioner have shown no effect in terms of readmission reduction (Kalogianni et al., 2016; Sawatzky et al., 2013), despite reduced rates of anxiety and improvements in health‐related quality of life. Discharge planning involves coordinating care to ensure a quality and safe transition from hospital to home (Bull et al., 2000). Inadequate discharge planning leaves patients ill‐equipped to manage their care after hospitalization (Boughton & Halliday, 2009; Bull et al., 2000) and increases re‐admission rates to hospital following discharge (Phillips et al., 2004; Shepperd et al., 2013). Effective discharge planning after cardiac surgery is crucial given the context of shortening LOS (Cowper et al., 2006) because an increased amount of care previously delivered in hospital is managed by patients and their families in their home environment (Bauer et al., 2009). However, that discharge planning needs to be co‐designed, patient focused and informed by patients’ narrative.

Following cardiac surgery, the trajectory of recovery requires discharge planning to be organized for three distinct phases of rehabilitation: immediate, intermediate and ongoing. In the immediate phase of rehabilitation, the aim of quality discharge planning is a timely discharge from hospital. During the intermediate phase the aim of quality discharge planning is to reduce unplanned re‐admission to hospital. The aim of quality discharge planning for the ongoing phase of rehabilitation is preparation of patients for long‐term self‐management of health (Shepperd et al., 2013). Robust evidence of the impact of patient participation in interventions for readmission reduction after cardiac surgery, is difficult to locate. In a qualitative study of providers and patients, a desire to participate in earlier conversations to allow time to develop plans for treatment and personal preferences, was expressed (Gainer et al., 2017). Patient participation is a quality indicator in healthcare and in the Australian setting ‘Partnering with Consumers’ is one of the eight National Standards for healthcare delivery. Patient participation is one aspect of care in the acute cardiac surgery context that has the potential to influence patient and surgical outcomes yet patients’ ability and willingness to participate is unclear (McTier et al., 2015). A key dimension of the patient quality and safety experience is being discharged from healthcare at the right time with the right plan (McElroy et al., 2016). Effective discharge planning should enhance patient understanding and engagement that in turn influences patients’ ability to participate in accessing and enacting post‐discharge care crucial to avoid readmission. Before we can tailor discharge planning interventions to suit the needs of this patient cohort there needs to be evidence to establish whether improved self‐efficacy enhances self‐management and as such, the capacity to make decisions that reduce the likelihood of representing to hospital or requiring readmission.

## THE STUDY

2

### Aims

2.1

The primary aim of this study is to investigate the effect of an mHealth intervention on recovery, as indicated by representation and readmission rates after adult cardiac surgery. Secondary aims are to assess the effect of the mHealth intervention on quality of life, knowledge, skill and confidence for self‐management using the patient activation measure.

### Hypothesis

2.2

We hypothesize that the mHealth intervention being tested will enhance patients’ self‐efficacy that will in turn reduce the likelihood of them representing to hospital or requiring readmission for recovery challenges that could be self‐managed.

### Design and procedure

2.3

A multisite, parallel group, pilot randomized controlled trial will be undertaken. A pilot study is necessary to determine sample size requirements for a fully‐fledged trial. The enrolment, intervention and assessment schedule is illustrated in Table 1. Placement on the surgical waiting list and surgical scheduling for each participating site takes place via telephone consultation with a liaison nurse. At the time of referral and placement on the surgical waiting list, verbal consent for participation will be sought and demographic data along with preoperative measures will be entered into a REDCap (Harris et al., 2009) recruitment log. The liaison nurse will contact an independent off‐site research assistant (RA‐1) to confirm participant recruitment via telephone or email. RA‐1 will allocate the patient to intervention or control.

**TABLE 1 jan15104-tbl-0001:** Schedule of enrolment, intervention and outcome assessment

Timepoint	Enrolment	Allocation	Study period				
			Surgery	Assessment			Close‐out
	*−t* _1_	0	*t* _1_	*t* _2_	*t* _3_	*t* _4_	*t* _5_
Enrolment							
Eligibility screen	X						
Informed consent	X						
Allocation		X					
Interventions							
Preoperative bundle		X					
Intermediate bundle			X				
Ongoing bundle				X			
Assessments							
EQ5D‐5L, PAM	X						
EQ5D‐5L, PAM, representation, readmission				X	X	X	
Mortality							X

Abbreviations: EQ5D‐5L, EuroQol short form quality of life assessment tool; PAM, patient activation measure; *t*
_1_, days 1–7 after hospital discharge; −*t*
_1_, placed on surgical waiting list; *t*
_2_, 30 days after surgery; *t*
_3_, 60 days after surgery; *t*
_4_, 90 days after surgery; *t*
_5_, 12 months after surgery.

The liaison nurse will also contact RA‐2, a specialist cardiothoracic clinical nurse, to confirm participant discharge. At 30‐, 60‐ and 90‐days all study participants will be contacted via telephone by RA‐2 to ascertain whether or not they have represented to hospital or have been readmitted to hospital, and if so why. At the time of these calls, postoperative assessment measures will be completed and entered directly into REDCap by RA‐2.

### Sample and recruitment

2.4

Participants will be recruited from The Royal Melbourne Hospital (RMH) Victoria, Westmead or Liverpool hospitals, in NSW. The two NSW sites service a similar demographic to RMH. The RMH provides services to the western and northern suburbs of Melbourne, extending to Shepparton, Bendigo, Ballarat and Horsham. The RMH provides specialist services including adult congenital cardiac surgery and has an international reputation in valvular surgery and total arterial revascularization. Annually there are approximately 600 cardiac surgery cases performed at this site. The Western Sydney Local Health District (WSLHD) in NSW is the second most populous and has one of the fastest growing populations, expected to increase by almost half a million people by 2036. The catchment includes more than 120 suburbs, over a million residents and the healthcare provided equates to more than $1.8 billion dollars annually. In this district more than 600 cardiothoracic procedures are performed at Westmead hospital annually. Similarly, the South West Sydney Local Health District (SWSLHD) will have over a million residents by 2021, an increase of 21% since 2011. The population is culturally diverse and the district houses some of the poorest communities in NSW. Liverpool Hospital performs between 350 and 400 cardiothoracic procedures annually.

The liaison nurse at each site leads initial contact with patients and placement on elective surgical waiting lists following referral receipt. They explain next steps and processes for preoperative preparation for surgery. They are also the point of contact for patients and families in the lead up to a date being booked for surgery and after the booking is confirmed. Waiting times on elective surgical lists are variable but most cardiac surgery cases are classified as either category 1 or 2 patients, with a median waiting time of 16–19 days in 2017–2018 (AIHW, 2018). At the conclusion of the usual care discussion the liaison nurse will ask elective patients if they are interested in participating in the study using a pre‐prepared script. If patients agree to participate, they will be informed that there will be no difference in the hospital care they receive and that an information form will be sent to them explaining the study. In addition, the nurse will explain that the study involves being randomized to receive a text/email link to GoShare, so they may or may not get the link, and there will be a series of follow‐up phone calls.

Inclusion criteria are any adult (>18 years of age) undergoing elective CABGS, valve surgery, CABGS and valve or aortic surgery, discharged home in 30 days, able to understand spoken English, and they own and use a smartphone, tablet or computer. Exclusion criteria are patients 18 years of age or younger, patients undergoing thoracic, transplant or non‐elective surgery, not discharged in 30 days, not discharged to their home/primary residence, and unable to understand spoken English without an interpreter.

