The GoShare cardiac surgery bundles have patient narrative videos focused on receiving a diagnosis that requires surgical intervention and preparing for heart surgery, intermediate recovery after heart surgery and ongoing recovery after heart surgery. The videos are delivered by a mixture of male and female patients representing young to older adults. The patients in the videos do not discuss specifics of surgery or medical management, the focus is on strategies for self‐help and self‐efficacy in managing the cardiac surgical experience. The information sheets in the bundles link to resources such as those provided by the Australian Centre for Heart Health and the National Heart Foundation. In the bundle homepage there is an option for patients to provide feedback. To date the cardiac surgery bundle, whilst available for use, has not been tested for effect. Scheduled messaging for the mHealth intervention, as per patient preference via email or SMS, will take place at the time of randomization. The preoperative intervention bundle link will be sent once randomized. On the day of discharge from hospital after surgery, liaison nurses will contact RA‐1 to confirm discharge and trigger distribution of a link to the postoperative immediate recovery bundle in 7 days of discharge. The intermediate recovery bundle link will be sent in 30 days of the day of surgery.

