### Outcome measures

2.6

This prospective multisite pilot study has been designed to test the effect of the cardiac surgery bundle on recovery as measured by representation and readmission rates in the intermediate and ongoing phases of rehabilitation from heart surgery. When readmission rates have been explored, a positive linear relationship with time after surgery is evident (Slamowicz et al., 2008). The primary outcome measures for this trial are representation and readmission in 30, 60, 90 days and at 12 months post surgery (reported separately). Readmission is a proxy for poor patient recovery and rates at 30 days are approximately 14% for isolated CABGS, incrementally increasing for valve, and CABGS with valve, respectively in Australian (Leppin et al., 2014) and international settings (Sun et al., 2008). Recent research emphasis the need to distinguish between representation and readmission that in combination occur in almost 27% of patients (Fox et al., 2013). Secondary outcomes include quality of life as measured by the short form EuroQol (EQ5D‐5L) (Brooks, 1996), and knowledge, skill and confidence for self‐management using the patient activation measure (PAM) (Hibbard et al., 2005). These measures will be assessed at baseline following enrolment and each time the primary outcome is assessed.

Testing in the pilot phase will enable sample size calculation based on the rate of 30‐day readmission to determine adequate power necessary for an ongoing prospective trial. Power analysis will be based on the assumption that readmission rates will be lowest at 30 days. Ongoing interim analyses will be undertaken to assess intervention effect on representation rate that is poorly reported, particularly in the Australian context. To be 95% confident that the readmission rate is in 10%, assuming 15% of the population will be readmitted, a total sample size of 49 patients is required. Loss to follow up, as indicated by 30‐day outcomes captured in the Australian and New Zealand Cardiac and Thoracic Surgeons (ANZSCTS) Database Registry, is approximately 4% annually. Each site performs an average of 10–15 cases per week. The aim is to recruit 20 patients from each site to a total of 60 patients, allowing for loss to follow up, prior to interim analyses in this pilot study. If two patients per week from each site can be recruited the trial should take approximately 10–12 weeks.

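### Actual discharge home within 30 days is an eligibility criterion, yet patients are randomised and sent the first bundle before surgery, so applying it as written excludes patients after allocation

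*Protocol article*

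**What the plan says.** The inclusion criteria (Protocol article, Sample and recruitment) require patients to be "discharged home in 30 days, able to understand spoken English". The exclusion criteria mirror this with "not discharged in 30 days, not discharged to their home/primary residence". Both are worded as facts about the discharge, not as an expectation, and the start of the 30 days is not given.

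The sequence is set out elsewhere:

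- Design and procedure: "At the time of referral and placement on the surgical waiting list, verbal consent for participation will be sought". Once recruitment is confirmed, the off-site research assistant "will allocate the patient to intervention or control". Table 1 puts the eligibility screen and consent at waiting-list placement and allocation at time 0, ahead of surgery.
- Intervention: "The preoperative intervention bundle link will be sent once randomized".
- Sample and recruitment: "most cardiac surgery cases are classified as either category 1 or 2 patients, with a median waiting time of" 16 to 19 days.

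On the link with the outcome, the Background states: "Postoperative LOS is an independent predictor of readmission irrespective of postoperative complications". On numbers, Outcome measures says: "The aim is to recruit 20 patients from each site to a total of 60 patients, allowing for loss to follow up". The allowance named is for loss to follow-up, about 4%.

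**The concern.** The only scheduled eligibility screen cannot be completed when it takes place. Whether a patient goes home within 30 days is settled after allocation and after the intervention has begun. If the criterion is then enforced, it removes patients who stay long, go elsewhere or die in hospital. Those are poor recoveries, in a trial that treats readmission as a marker of poor recovery.

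Two things are at stake. First, if the preoperative bundle changes who goes home in time, the exclusions differ by arm and the comparison loses the protection of randomisation. The assistant who holds the allocation is also the person told of each discharge, so enforcement is not clearly separated from knowledge of the arm. Second, even with equal exclusions in both arms, the pilot's 30-day readmission rate is meant to size the main trial. A rate from a selected subset describes a different population from the one that would be randomised.

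**Working it through.** **Order of events.** Screen and consent (waiting list), then allocation (time 0), then preoperative bundle (at randomisation), then surgery (median wait 16 to 19 days), then discharge. The criterion depends on the last step and eligibility is screened at the first. This part needs no arithmetic.

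**The plan's own sample size.** Inputs from Outcome measures: 15% readmission, margin read as ±10 points, 95% confidence.

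n = 1.96² × 0.15 × 0.85 / 0.10² = 48.98, so 49. The stated figure reproduces. Allowing for 4% loss, 49 / 0.96 = 51.04, so 52, within the 60 planned.

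**Room for exclusions.** Number analysed = 60 × 0.96 × (1 − x), where x is the share excluded after randomisation. The protocol does not give x, so it is varied here. Half-width = 1.96 × √(0.15 × 0.85 / number analysed).

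| x | Analysed | 95% half-width (points) |
|---|---|---|
| 0% | 57.6 | 9.2 |
| 5% | 54.7 | 9.5 |
| 10% | 51.8 | 9.7 |
| 15% | 49.0 | 10.0 |
| 20% | 46.1 | 10.3 |

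The number falls below 49 once x exceeds 1 − 49/57.6 = 14.9%.

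**Possible bias with no true effect on readmission.** All inputs except the 15% are assumptions:

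- e: share not home by day 30 without the bundle, 5% to 15%
- h: readmission risk in those patients, 30% to 40%
- f: fraction of them whom the bundle moves to timely home discharge, 0 to 50%

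The risk in the remainder is l = (0.15 − e × h) / (1 − e). After exclusion the control arm shows l. The intervention arm shows [(1 − e) × l + f × e × h] / [(1 − e) + f × e].

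- e = 10%, h = 40%, f = 50%: l = (0.15 − 0.04)/0.90 = 12.2%. Intervention = (0.11 + 0.02)/0.95 = 13.7%. Difference about 1.5 points against the intervention.
- Smallest non-zero case (5%, 30%, 25%): 14.2% v 14.4%, 0.2 points.
- Largest case (15%, 40%, 50%): 10.6% v 13.0%, 2.4 points.
- f = 0: difference zero, but the observed rate in both arms falls from 15% to between 14.2% (e = 5%, h = 30%) and 10.6% (e = 15%, h = 40%).

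**Comparison with sampling error.** With 30 per arm and 15% readmission, the standard error of the difference is √(2 × 0.15 × 0.85 / 30) = 9.2 points, and the 95% half-width is about 18 points. The largest illustrated bias is about a quarter of one standard error (2.4/9.2 = 0.26).

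**A limit on the direction.** The illustration assumes that excluded patients have time at risk and a higher risk. The outcome windows run from surgery, so a patient still in hospital at day 30 cannot have been readmitted by then. For that group, exclusion would raise the 30-day rate. The downward shift in the 30-day rate therefore comes from patients discharged elsewhere, or discharged with time left at risk. For long-stay patients it can appear only in the later windows.

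**The case against.** The strongest objection is that no sentence says randomised patients are dropped from the analysis. Every participant is to be telephoned at 30, 60 and 90 days, data already collected from patients who withdraw are kept, and the single screen on the waiting list could mean that anticipated discharge was intended. Analysis sets are commonly left to an analysis plan, which is not shown. This stands in part. A reader might infer that the analysed arms will certainly differ from the randomised arms, and the documents do not go that far. But the criteria are worded as outcomes of the admission, nothing says that patients who fail them remain participants, and an exclusion criterion has no other stated use.

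Three further inferences are tempting and not supported:

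- **That elective status is also a post-randomisation criterion.** The liaison nurse approaches patients who are on elective lists, so this reads as a screening rule. No later re-check is described.
- **That the sample size is inadequate.** The 60 planned leaves a margin of eight over the 52 needed after loss, and the exclusion rate is unknown.
- **That a bias of some particular size has been shown.** The bundle's effect on discharge is not known. The videos are described as avoiding surgical and medical specifics, and the platform did no better than usual care in another population. If discharge is unaffected, the expected between-arm bias is zero.

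It is also fair to say that this is a pilot. Its primary aim is nonetheless stated as the effect on representation and readmission, and its interim analyses are to assess that effect.

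**Conclusion.** The timing defect holds on the face of the document: eligibility rests on an event after allocation, after the intervention has started, and of a kind that the protocol links to readmission. Enforced as written, it takes randomised patients out. Whether this biases the comparison depends on the bundle affecting discharge, which cannot be judged from the documents. The assumed range of 0.2 to 2.4 points is small beside a standard error of about 9.2 points. The effect on the planning rate does not need a treatment effect, but it does need excluded patients to differ in risk, with the caveat above on those still in hospital at day 30. The stated precision is lost only if exclusions reach about 15%. The case for changing the text rests on validity and clarity, not on a demonstrated numerical distortion or a shortfall in patients.

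**What to change.** 1. Restrict eligibility to facts known before randomisation, or reword the discharge criterion as expected discharge home within 30 days, judged at screening. State when the 30 days begin.
2. State that all randomised patients are analysed in the arm allocated, on the existing windows counted from surgery. Restarting the windows at discharge would redefine the primary outcome and again condition on surviving to discharge. Limiting the analysis to operated patients would also be a post-randomisation condition.
3. Report by arm the numbers not operated on, dying in hospital, staying beyond 30 days and discharged elsewhere.
4. Show the subset discharged home within 30 days only as a sensitivity analysis.

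The cost is amendment wording and a few more patients in the calls already planned. The price in interpretation is a slightly more mixed population and a few patients with little or no time at risk of readmission, which the by-arm reporting makes visible. The change is best made before enrolment, because patients removed and not followed cannot be recovered later.
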